### Concealment mechanism {16b}

An independent person who is not involved in the trial will label supplement packs as A and B. Both the investigators who are performing the study and participants will be blinded to the intervention allocation. Additionally, the allocation sequence will be concealed from those who are assigning participants to the intervention groups using opaque sealed envelopes. Randomization codes will be unlocked after the trial completion.

### Implementation {16c}

Participants will be allocated to either the selenium or placebo group by an independent investigator who is not involved in the study. The allocation process will be monitored by a second researcher (OS).

## Assignment of interventions: Blinding

### Who will be blinded {17a}

The current study will have a double-blind design, which means that both the investigators who are performing the study and participants will be unaware of group allocation.

### Procedure for unblinding if needed {17b}

Labels on supplement packs will be revealed only after the study completion. However, based on the criteria of the Medical Ethics Committee, unblinding is allowed in case of any adverse events to determine whether the patient received selenium or placebo. If so, it will be recorded and reported in the Iranian Registry of Clinical Trials, and the Ethics Committee of Isfahan University of Medical Sciences, as well as results of the study. Further information will also be collected to decide whether those who reported adverse side effects should be excluded.

## Data collection and management

### Plans for assessment and collection of outcomes {18a}

#### Demographic variables

A general self-administered questionnaire will be used to assess participants’ demographic characteristics, including age, sex, marital status, education, medical history and their medications, family history of migraine, supplementation, and smoking at the beginning of the study. Moreover, the socioeconomic status of subjects will be evaluated through specifically designed questions such as the number of family members, home or car ownership, and participant’s job using a self-administered questionnaire.

#### Migraine symptoms assessment

An expert neurologist will assess migraine characteristics, including severity, frequency, and duration of migraine attacks. Headache severity will be assessed using a visual analogue scale (VAS) questionnaire on a 0–10 scale with 0 representing "no pain" and 10 "the worst imaginable pain”. The Persian version of this questionnaire, validated by previous investigators, will be used [21]. The patients will note the feeling that represents their perception of pain. The frequency and duration of migraine headaches will be evaluated as the number of attacks per month and the mean duration of attack in each day, respectively.

#### Dietary intake assessment

Six dietary recalls (four weekdays and two weekend days) will be obtained from all participants at weeks 2, 4, 6, 8, 10, and 12. All participants will be asked to report their dietary intake based on household measures. Then, these reports will be converted to grams using standard protocols [22]. To calculate nutrient intake throughout the trial, we will use the United States Department of Agriculture (USDA) nutrient databank.

#### Physical activity assessment

In addition, two 1-day physical activity (PA) records (including a working day and a non-working day) will be collected from all participants at weeks 2 and 8. PA levels will be reported as metabolic equivalent hours per day (MET/h/day).

#### Anthropometric measures and blood pressure

Body weight will be measured to the closest 100 g using a digital scale at the state of minimum clothing and without shoes. Height will be assessed to the nearest 1 mm using a non-stretched tape in a standing position with no shoes. Waist circumference (WC) will be measured to the nearest 1 mm at the midpoint between the lowest rib and the iliac crest, with the subject standing, after a normal exhalation. Body mass index (BMI) will be calculated as weight in kilograms divided by height squared in meters. Blood pressure (BP), including systolic and diastolic BP, will be assessed using a standard sphygmomanometer. Measurements will be taken twice, and the average value will be reported as the final BP.

#### Assessment of quality of life

There is some evidence indicating that quality of life is impaired in migraine patients [23]. In the present study, we will use two widely used questionnaires, including the Headache Impact Test (HIT-6) and the Migraine-specific Quality of Life (MSQ), to investigate the effect of selenium supplementation on the participants’ quality of life. As different aspects of functioning are examined in each questionnaire, using these two concurrently is common in clinical trials [24, 25]. These questionnaires have been translated into Persian by prior investigators, with their validity and reliability confirmed among Iranian adults [26, 27].

The HIT-6 questionnaire evaluates the influence of headaches on migraine patients’ well-being and daily performance [28]. This questionnaire includes six items, each with five response options, scored between 6 and 10, including never (six points), rarely (eight points), sometimes (10 points), very often (11 points), and always (13 points) options. The total score of HIT-6 ranges from 36 to 78. It is categorized as no impact (36–49), moderate impact (50–55), substantial impact (56–59), and severe impact (≥ 60) on patients' quality of life.

The MSQ (version 2.1) explores the impact of migraine headaches on patients’ daily functioning over the past four weeks [29]. This questionnaire has three domains: 1) role restrictive domain describing the reduction of daily activities (7 items), 2) role preventive domain describing the influence of migraine headaches on normal work and social activities (4 items), and 3) emotional functioning domain that evaluates the emotions associated with headache (3 items). Each item includes six response options, scored between 1 and 6: none of the time (score 1), a little bit of the time (score 2), some of the time (score 3), a good bit of the time (score 4), most of the time (score 5), and all of the time (score 6).The total score of each domain is computed as a sum of item responses and rescaled from 0 to 100, where higher scores indicate better quality of life.

#### Mental health assessment

To assess psychological disorders, a 21-item Depression, Anxiety, and Stress Scale (DASS-21) will be used [30]. The validity and reliability of the Persian version of this questionnaire have been also approved by Samani et al. [31]. Each subscale (depression, anxiety, and distress) consists of seven questions, with responses rated from 0 (does not apply to me at all) to 3 (applies to me most of the time). Subscale scores range from 0 to 21, with higher scores indicating increased psychological distress. To align with DASS-42, subscale scores will be multiplied by two for interpretation.

### Plans to promote participant retention and complete follow-up {18b}

To enhance participant retention, the potential health benefits of selenium will be discussed, and regular telephone contact by the principal investigator (AB) will be maintained.

### Data management {19}

Data coding, security, and storage will be monitored by one of the researchers. Electronic data entry will occur at the participating site, with secure storage of forms. Data entry and values will undergo double-checking.

### Confidentiality {27}

Each participant will receive a unique identification code to store research data. The code list will be accessible only to researchers and protected by the principal investigator throughout the trial. Participants’ personal details will remain confidential in all publications.

### Plans for collection, laboratory evaluation, and storage of biological specimens for genetic or molecular analysis in this trial/future use {33}

A 5 ml blood sample will be collected at the baseline and end of the intervention. The serum will be obtained by centrifugation immediately after sample collection, then will be maintained at -80 degrees Celsius for future tests. NO levels will be measured by the Griess method, serum levels of TAC by the CUPric Reducing Antioxidant Capacity, TOS by the modified Ferrous Oxidation-xylenol Orange, and MDA levels by the Thiobarbituric acid reactive substance using commercial kits (Kiazist Life Sciences, Iran).

## Statistical methods

### Statistical methods for primary and secondary outcomes {20a}

To examine normal distribution of variables, the Kolmogorov–Smirnov test will be used. To normalize the non-normally distributed variables, we will conduct a log transformation. The intention-to-treat (ITT) approach will be used to estimate missing values on outcome variables. Independent sample t-test will be used to detect differences in quantitative variables between intervention and control groups. For the assessment of qualitative variables between the two groups, the chi-square test will be performed. The paired-sample t-test will also be used to examine within-group differences. One-way analysis of covariance (ANCOVA) will be performed to detect the effect of selenium supplementation on outcome variables. In this analysis, potential confounders will be taken into account. All statistical analyses will be conducted using the SPSS software version 21 (SPSS, Inc. Chicago, IL, USA). P-values less than 0.05 will be considered statistically significant.

### Interim analyses {21b}

No interim analyses are planned for the present study; however, immediate study cessation will occur for those with adverse side effects. These adverse side effects include death, disability, and severe allergic reactions, which have a significant impact on the patient's health. However, as the ITT analysis will be performed, participants who drop out will also be included in data analysis.

### Methods for additional analyses (e.g., subgroup analyses) {20b}

No subgroup analyses are planned. ANCOVA will be performed to detect the effect of selenium supplementation on outcome variables, which will be adjusted for variables that significantly differ between the selenium and placebo groups.

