## Assignment of interventions: Allocation

### Sequence generation {16a}

After recruitment, stratified block randomization will be performed based on participants’ age (18 to 39 and 40 to 65 years) and sex (male or female) across the two groups. Then, within each of the aforementioned strata, eligible participants will be randomly assigned in a 1:1 ratio to receive either selenium or placebo. Balanced randomization will be generated using an online tool (https://www.sealedenvelope.com/simple) by a person who is not involved in the study. Participants in the intervention group (*n* = 36) will receive a tablet containing 200 µg selenomethionine daily, while the placebo group (*n* = 36) will receive a tablet containing 200 µg starch daily.

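### The ANCOVA covariates are to be chosen by between-arm significance, and nothing commits the plan to the baseline outcome or the stratification factors; followed literally, this costs precision.

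*Protocol article*

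**What the plan says.** The selection rule stands in the protocol article under Methods for additional analyses {20b}. The ANCOVA used to detect the effect of selenium is one "which will be adjusted for variables that significantly differ between the selenium and placebo groups". The main analysis section, Statistical methods for primary and secondary outcomes {20a}, names the same ANCOVA and says of covariates only this: "In this analysis, potential confounders will be taken into account". The confounders are not named.

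Other sections bear on the point:

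- The only significance threshold is in {20a}: "P-values less than 0.05 will be considered statistically significant". The between-arm test there is not tied to a time point: "Independent sample t-test will be used to detect differences in quantitative variables between intervention and control groups".
- Sequence generation {16a} stratifies the randomisation by age (18 to 39, 40 to 65) and sex.
- The Abstract says that the outcomes are measured at baseline and at the end of the study.
- Dietary recalls "will be obtained from all participants at weeks 2, 4, 6, 8, 10, and 12", and physical activity records "will be collected from all participants at weeks 2 and 8". No baseline measurement of either is described.

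**The concern.** A covariate earns its place in an ANCOVA by predicting the outcome. A between-arm p-value does not measure that. Under randomisation it picks up chance imbalance only, so a strong predictor that happens to be balanced is left out and an irrelevant variable that happens to be imbalanced is put in. The best available predictor of a final value is usually the same measure at baseline, and the rule gives it no standing of its own. Age group and sex are balanced by the stratified design and would almost never pass the screen. If they are prognostic, leaving them out makes the standard errors too large.

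Two things are at stake: precision in a trial of 72 patients, and a model that is settled only after the data are tested. A third point is narrower. The rule is not restricted to baseline variables, so its wording would admit diet or activity recorded after treatment began. Adjusting for a variable that treatment may have affected can bias the estimated effect.

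**Working it through.** **The plan's own figure.** The protocol gives no power figure for the ANCOVA. Its sample size (Sample size {14}) is an unadjusted comparison of two means, n = 2(a + b)²σ²/(μ1 − μ2)², stated as 33 per arm, with difference 1.4 − (−0.13) = 1.53 and σ given as 4.00.

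- 4.00 as SD: 2 × 2.802² × 16 / 1.53² = 107.3, so 108 per arm.
- 4.00 as variance: 2 × 2.802² × 4 / 1.53² = 26.8, so 27 per arm.

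Neither gives 33. That is a separate matter, but it means that the protocol fixes no single standardised effect: 1.53/4 = 0.38 SD or 1.53/2 = 0.77 SD. The check below assumes 0.5 SD, which lies between them.

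**How often the rule selects the baseline outcome.** With a 0.05 screen and randomised arms, a given baseline variable passes in about 5% of trials. Simulation of 20,000 trials per setting gave 4.7% to 5.2%. If k independent variables are screened, the chance that at least one is selected spuriously is 1 − 0.95^k: 40%, 64% and 79% for k = 10, 20 and 30. The protocol does not give k.

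**Power.** Assumptions: 36 per arm (the recruited number, before dropout), effect 0.5 SD, two-sided 5%, and r from 0.3 to 0.7. In the normal approximation, power = Φ(0.5 × √(36/2) / k − 1.96) = Φ(2.121/k − 1.96), where k is the residual SD relative to the outcome SD:

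- final value, unadjusted: k = 1, so Φ(0.161) = 56% at any r;
- change score, unadjusted: k = √(2(1 − r)) = 1.183, 1.000, 0.775, so 43%, 56%, 78%;
- baseline always in the model: k = √(1 − r²) = 0.954, 0.866, 0.714, so 60%, 69%, 84%.

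The rule omits the baseline value about 95% of the time, so its power should sit close to the unadjusted figures. Simulation confirms this:

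| r | Final value: rule vs always adjusted | Change score: rule vs always adjusted |
|---|---|---|
| 0.3 | 56% vs 59% | 43% vs 60% |
| 0.5 | 56% vs 67% | 55% vs 66% |
| 0.7 | 57% vs 83% | 78% vs 83% |

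With the baseline value in the model, both scales give the same test, so the small differences between the two always-adjusted columns are simulation error. The gap is 3, 11 and 26 points for final values and 17, 11 and 5 points for change scores.

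**A second setting.** With 33 per arm and an SD of 2.218, back-solved so that the unadjusted test has 80% power for 1.53, final-value power under the rule versus always adjusted is 79.2% vs 81.7%, 79.9% vs 88.5% and 80.9% vs 96.7% at r = 0.3, 0.5 and 0.7.

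**Type I error.** Across the runs the rule gives about 0.034 to 0.046, against about 0.05 with fixed adjustment. The reason is that the baseline value enters the model mainly in the imbalanced trials where an unadjusted test would tend to reject falsely, while the remaining trials keep a standard error that is too large.

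**The case against.** The strongest reply is that the text does not say that only significantly different variables enter. The sentence sits under additional analyses, the main section has no significance filter, and an ANCOVA needs at least one covariate. The authors may intend a baseline-adjusted ANCOVA plus any imbalanced variables. If so, the power loss computed here disappears. This stands as a limit on the size of the problem. It does not rescue the rule: no section names the baseline outcome as a covariate, {20b} describes the same ANCOVA as {20a}, and its criterion is the only one given.

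It may also be said that a condensed article can leave the covariate list to a fuller document. That holds for a missing list. It does not cover a criterion that the article itself states.

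Four stronger readings are tempting and not supported:

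- A reader might infer that false positives are inflated. With the baseline outcome as the screened variable, the error rate is below 5%.
- A reader might take the 26-point loss as the cost. It is the high end of one assumed analysis; at r = 0.3 with final values the loss is about 3 points. The negative planning mean for malondialdehyde suggests change scores, for which the loss is largest at low r instead.
- A reader might infer that the protocol plans to adjust for on-treatment diet or activity. No section says so, and since {11a} asks participants to keep both unchanged, the records may serve only to monitor that.
- A reader might say that omitting the strata invalidates the analysis. The effect is conservative standard errors, and only if age or sex is prognostic, which the protocol does not show.

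**Conclusion.** The point holds as a badly fixed rule. The protocol states a significance-based criterion for the covariates of its efficacy ANCOVA and commits to neither the baseline outcome nor the stratification factors. Followed literally, it costs roughly 3 to 26 percentage points of power, depending on r and on whether final values or change scores are analysed; at r = 0.5 the cost is about 11 points on either scale. These sizes rest on 36 per arm, an assumed 0.5 SD effect and an assumed r of 0.3 to 0.7, and on the baseline value not being added regardless of the rule. The possible adjustment for on-treatment diet or activity is an ambiguity to close. The harm shown is lost precision and a data-dependent model, not an invalid test, so this should be fixed but does not by itself undermine the trial.

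**What to change.** Before unblinding, replace the sentence in {20b} and the reference to potential confounders in {20a} with one model for every continuous outcome:

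week-12 value = arm + baseline value of that outcome + age stratum (18–39, 40–65) + sex.

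Remove between-arm significance as a way of choosing covariates. State that diet and physical activity recorded during treatment are reported by arm descriptively and do not enter the model.

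The cost is a short amendment to two sections and three degrees of freedom. All the variables are already collected. Concealment mechanism {16b} keeps the randomisation codes locked until the trial is complete, so the change can be made without knowledge of the results.

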### Methods in analysis to handle protocol non-adherence and any statistical methods to handle missing data {20c}

In the present study, participants who drop out will not be excluded from the final analysis as an ITT method will be conducted. Missing data will be addressed by multiple imputations.

### Plans to give access to the full protocol, participant-level data, and statistical code {31c}

The corresponding author will make datasets, statistical code, and the complete protocol available upon reasonable request.

## Oversight and monitoring

### Composition of the coordinating center and trial steering committee {5d}

The principal researcher coordinates the study, with regular communication among the study team and supervision by a steering committee. Furthermore, the Ethics Committee of Isfahan University of Medical Sciences will ensure adherence to ethical principles, and study will be modified or terminated in case of ethical violations.

### Composition of the data monitoring committee, its role, and reporting structure {21a}

Data monitoring will be conducted impartially and continuously by the academic committee of Isfahan University of Medical Sciences.

### Adverse event reporting and harms {22}

Based on previous studies, supplementation with 200 µg of selenium per day has been found to be safe. If any complications were reported with the selenium supplementation, the intervention will be immediately stopped, and the necessary medical measures will be taken.

### Frequency and plans for auditing trial conduct {23}

The present study will be conducted by the guidance of the Ethics Committee of Isfahan University of Medical Sciences. The quality, validity, and adherence to ethical standards will be monitored by this Committee during at least two monitoring sessions. In addition, a report will be submitted to the auditor every three months.

### Plans for communicating important protocol amendments to relevant parties (e.g., trial participants, ethical committees) {25}

Any changes to the study protocol details, including study sample size or methods, must be approved by the Ethics Committee of Isfahan University of Medical Sciences. Also, all changes will be reported at https://www.irct.ir/.

### Dissemination plans {31a}

Final findings and data will be presented in future publications.

## Discussion

There has been no globally approved treatment for migraine until now, presenting a considerable challenge for healthcare professionals [32]. The management of migraine is particularly complex due to its high prevalence and associated comorbidities, especially mental disorders [4]. Therefore, the development of safe, non-pharmacological, nutrient-based approaches for the management of migraine headaches is critical. Considering the beneficial effects of selenium in different neurological disorders, particularly those with inflammatory and oxidative nature, supplementation with this nutrient could be advocated as the potential strategy for the management of migraine headaches [12]. To the best of our knowledge, this is the first clinical trial evaluating the effect of selenium supplementation on migraine symptoms, psychological disorders, and biomarkers of oxidative stress in migraine patients.

The underlying rationale is based on the hypothesis that selenium may positively affect migraine symptoms through scavenging free radical species, particularly NO, and elevating antioxidant levels in the brain. In the past few decades, nutraceutical agents such as antioxidants have attracted much attention for migraine management. A limited number of studies have investigated the effects of various antioxidants on migraine symptoms, mostly reporting promising findings. For example, in one of these trials, nano-curcumin and coenzyme Q10 supplementation were shown to reduce the frequency, duration, and severity of migraine headaches [33]. Similar effects on the frequency and severity of headaches were also observed after supplementation with a combination of different antioxidants, including pine bark extract, vitamin C, and vitamin E, among migraine patients [34]. In addition, a recent clinical trial, in which the effect of vitamin C, E, and N-acetylcysteine co-supplementation on migraine patients was assessed, a significant reduction in headache frequency and duration was also reported [35]. Taken together, there is a need for a clinical trial investigating the effect of selenium supplementation on migraine symptoms and other clinical parameters of migraine patients.

